### Intervention

2.5

The guided internet-based stress management program (Rel@x) was developed by the authors on the basis of existing stress management techniques, and co-created with the university students to meet the specific needs of the students. We have conducted several focus group discussions and interviews with the students to understand their opinions about this program and their needs. We have tailored the program to align with their preferences. The stress management program is based on cognitive-behavioral therapy (CBT) and Lazarus and Folkman's transactional model of stress (Lazarus and Folkman, 1984). It comprises five modules that are delivered via computer, laptop, tablet, or mobile phone. Each module takes approximately 60 min to complete. Students will be advised to complete one module per week. Accordingly, the duration of the stress management program is approximately five weeks. However, participants can follow the program at their own pace. Every module consists of evidence-based information, exercises, fictitious examples, and homework assignments. The content is delivered in text format with pictures and infographics; some modules include video clips and audio recordings on a relevant subject. The intervention is available in both English and Dutch.

Modules cover information about stress, coping strategies, cognitive restructuring, and problem-solving skills. At the beginning of the intervention, an introduction module is provided. This introduction module gives general information about the use of the platform and the basics of the modules to set realistic intervention expectations. The first module covers information about stress, exercises about identifying the stressors and symptoms of stress, and the consequences of high levels of stress on health. The second module introduces the coping strategies (i.e. emotion-based coping, problem-based coping, and meaning-based coping) and the effect of perceived control over stressful situations. The third module includes psychoeducation on cognitive restructuring and several exercises to identify and challenge negative thinking patterns. In the fourth module, problem-solving steps are explained with the exercises. The last module includes a summary of each module, exercises to review the participant's progress, and setting goals for the future. Several tips are provided to transfer the information and strategies from the modules into everyday life.

Each module begins with a review of the homework assignment from the previous module and ends with a summary of the module. In addition to the main modules, there are four optional modules which students can select based on their needs. The topics of the optional modules are 1) time management and procrastination, 2) assertiveness, 3) adaptation to a new culture, 4) sleep, emotional eating, and exercise. The optional modules are available at the end of each module.

### E-coaches

2.6

Participants receive feedback from the e-coaches after completing each module. E-coaches are (research) master students in clinical psychology and 3rd-year clinical psychology bachelor students (at the end of the 2nd semester) who meet the criteria of specific courses namely 1) coaching and assessment, 2) low-intensity treatments for common mental health problems, and 3) diversity in clinical practice. The e-coaches were selected in the following way: After attending an informative meeting, interested students responded in writing, outlining their motivation to be an e-coach in this project. Selected students were invited for an interview with the research team. After completing the selection, students completed 5 1/2 hours of training including a supervised intervision meeting during which the e-coaches discuss their feedback in a plenary session. These e-coaches are regularly supervised by the research team, including a clinical psychologist, for the duration of the intervention. E-coaches will provide asynchronous written personalized feedback to each participant via the intervention platform. The written feedback aims to increase motivation and adherence. Participants also receive automatic reminders to increase engagement in cases of two weeks of inactivity.

### Platform

2.7

The intervention is delivered via the Caring Universities platform. This platform has been developed for e-health applications for college students in the Caring Universities project and includes other interventions on several issues for college students. On this platform, researchers can add and arrange intervention content, materials (e.g. video, visuals), and questionnaires. Students and e-coaches can create an account and log on to the platform with a user name and self-generated password via laptops, tablets, and mobile phones. This platform is accessible 24/7 for the participants. After completing the intervention and outcome assessments, participants will still be able to access the platform. A stress journal and a single-item question to keep track of stress levels were integrated into the platform for self-monitoring. Moreover, the e-coach and student can send text messages to each other on this platform. The platform complies with the General Data Protection Regulation (GDPR).

### Assessment measures

2.8

#### Primary outcomes

2.8.1

##### Satisfaction with the intervention

2.8.1.1

Participants' satisfaction with the intervention is assessed by the Client Satisfaction Questionnaire (CSQ-8) (Larsen et al., 1979). This self-report questionnaire has been widely used to measure satisfaction levels with an online intervention. This questionnaire includes eight items on a 4-point scale. The total score ranges from 8 to 32 and a higher score indicates greater satisfaction. The psychometric properties of the scale showed high reliability and validity for the web-based interventions (Boß et al., 2016). The Dutch translation of the CSQ-8 also showed similar properties (De Brey, 1983).

##### Usability

2.8.1.2

The usability of the intervention is measured by the System Usability Scale (SUS-10) (Brooke, 1996). This scale consists of 10 items on a 5-point Likert scale. The total score can range from 0 to 100. Previous studies examining the reliability and validity of the scale showed promising results (Lewis, 2018). Although the Dutch translation of the SUS-10 has been used in previous studies (Wever et al., 2012), published psychometric properties of the scale in Dutch could not be retrieved. However, a comprehensive review of all studies using this scale indicated adequate reliability (Bangor et al., 2008).

#### Secondary outcomes

2.8.2

Secondary outcomes of this study are perceived stress, depression, quality of life, and adherence.

##### Perceived stress

2.8.2.1

The Perceived Stress Scale (PSS-10) is used to assess the stress levels (Cohen and Williamson, 1988a; Cohen et al., 1983). This scale is a brief, easy-to-use self-report scale containing 10 items on a 5-point Likert scale. The scale aims to assess the extent to which participants evaluate their life as unpredictable and uncontrollable. Higher scores indicate higher perceived stress. The PSS-10 is used to assess the changes from pre- to post-scores. In this study, we have also added the short version of the PSS-10 to track the stress levels of the participants on a weekly basis. The short version of this scale includes four items from the PSS-10. The PSS-4 is sent to the students to gain a deeper understanding of the process of change. The PSS-10 and the PSS-4 showed high reliability and validity (Cohen et al., 1983; Lee, 2012). The PSS yielded good psychometrics in college students (Denovan et al., 2019).

##### Depressive symptoms

2.8.2.2

The PHQ-9 is used to assess depression (Kroenke et al., 2001). Each item is rated on a 0–3 scale. Higher scores indicate a higher level of depressive symptoms. The scores of 1–4, 5–9, 10–14, 15–19, and 20–27 indicate no depression, mild depression, moderate depression, moderately severe depression, and severe depression, respectively (Kroenke et al., 2001).

##### Quality of life

2.8.2.3

Quality of life is measured by the EuroQol-5 Dimension-5 Level Scale (EQ-5D-5L) (Group TE, 1990). This scale has five dimensions namely mobility, self-care, usual activities, pain/discomfort, and anxiety/depression, with each dimension consisting of five levels indicating the severity of the problem. Psychometric studies of the EQ-5D-5L showed promising and robust results in several patient samples (Janssen et al., 2013; Herdman et al., 2011).

##### Adherence

2.8.2.4

Adherence is defined as the extent to which the individuals get involved in the intervention (Christensen et al., 2009). In the present study, adherence is measured primarily by the total number of modules completed by each participant at the post-test. The number of completed modules is divided by the total number of modules to calculate the completion rate. Moreover, we will assess other indicators of adherence, such as the time spent in the intervention, the number of logins, and the number of completed exercises.

#### Additional measures

2.8.3

##### Sociodemographic information

2.8.3.1

In order to examine the characteristics of the sample, sociodemographic information is collected such as age, gender, ethnicity, university, faculty, marital status, and whether they are receiving psychological treatment (psychotherapy or medication).

##### E-coach evaluation

2.8.3.2

We also ask participants to evaluate the e-coach using the Working Alliance Inventory for guided internet interventions (WAI-I) (Martín et al., 2020). This inventory contains 12 items on a 5-point Likert scale with two dimensions: task & goal agreement with the therapist and bond with the therapist. The WAI-I measures the perceived collaboration with the therapist from the perspective of the patient. The psychometric characteristics of the WAI-I yielded adequate results (Martín et al., 2020).

##### Evaluation of each module

2.8.3.3

After completing each module, participants are asked to give feedback about the appropriateness of the modules for the college student sample. The questions about the evaluation of the modules were derived from another study (Rahmadiana et al., 2019). Participants are asked the following questions: 1) Were the goals of this Internet module clearly defined? 2) Was the content in this module clear and easy to understand? 3) Was this module easy to navigate? 4) Was the length of this module appropriate to the topic? 5) Were the illustrated pictures in this module helpful? 6) Did you understand the language, idiom, and words used in this module? 7) Do you think the case examples given in this module were appropriate for university students? We also ask three open-ended questions as follows: 1) What did you learn from this module? 2) Is there anything you would want to change in this module? 3) Is there anything you want to mention about this module?

Moreover, if feasible, we will explore possible stressors based on the answers of participants in the questions and exercises of the intervention.

#### Semi-structured interviews

2.8.4

We conduct in-depth interviews with a selection of at least 10 participants among the students who complete all main modules. The selection of the participants is based on the maximum variation sampling, taking into account equal representation of gender groups, varying levels of satisfaction with the program (CSQ-8), usability (SUS-10), and the changed scores of perceived stress (PSS-10) from pre-test to post-test. We select some students showing little or no improvement and some students with greater improvement in perceived stress. Similarly, we select a few students who show low satisfaction and a few students with high satisfaction with the program. Semi-structured interviews are conducted with a set of questions based on previous studies to examine the user experiences in a newly developed Internet-based intervention (Devi et al., 2014; Fleischmann et al., 2018). The original questions have been revised to fit the purpose of our study: 1) What were your initial thoughts and feelings regarding this Internet-based stress program? 2) Why did you prefer this program as an internet-based treatment over face-to-face support? 3) How was your overall experience of using the program? 4) Do you feel anything has changed in your life since using the program? 5) Generally, how did you feel about this program? 6) To what extent did you accept the program and why? 7) Were there any enjoyable parts in the program? (And why?) 8) What was your experience of the program being online and delivered via the internet? 9) How did the program fit in with your lifestyle? 10) Is there anything you would want to change or add to this program?

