Although college students experience high levels of stress, the utilization of campus mental health services is remarkably low due to several barriers (Ebert et al., 2019; Rosenthal and Wilson, 2008). Lack of perceived need for receiving help, preference for self-help, perceived stigma, negative attitudes toward the treatment, lack of time, and not being aware of the services at the campus are among the most important treatment barriers (Czyz et al., 2013; Eisenberg et al., 2007). In addition, cultural differences and language barriers were among the main reasons reported for the low uptake of on-campus counseling services by international students (Eisenberg et al., 2007; Hyun et al., 2007; Mori, 2000). Apart from the attitudinal barriers, system-related circumstances can also limit access to mental health support; these include long waiting lists and insufficient resources to meet the increased demands on counseling centers at universities (Watkins et al., 2012).

E-health interventions can be helpful in overcoming some of the aforementioned treatment barriers. The internet is used by college students for various purposes, including maintaining contact with friends or family members, building a social network, getting acquainted with the new university environment, educational reasons (Gray et al., 2010; Sleeman et al., 2016), and also for seeking health information (Horgan and Sweeney, 2010). Internet-based interventions could, therefore, be easily adopted by this population. Besides, internet interventions have additional benefits such as anonymity, flexibility in time, and easy, low-cost access to mental health support (Andersson and Titov, 2014; Ebert et al., 2017; Stallman and Kavanagh, 2018). Universities can also alleviate the growing demand for university counseling centers by offering internet interventions to their students.

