### Eligibility criteria

2.4

We include participants if they meet the following criteria: 1) aged 16 or older, 2) having enrolled as bachelor, master, or Ph.D. student, 3) having elevated levels of perceived stress (PSS-10 ≥ 20.4) at screening, 4) having given informed consent. Both domestic and international students are eligible to participate in the study.

There is no established cut-off score for the PSS-10. Following the procedures of previous studies in this field, we decided to use 20.4 as a cut-off score in our study calculating the one standard deviation (*SD* = 6.2) above the mean score of 14.2 which has been found in a general population sample between 18 and 29 years old (Cohen and Williamson, 1988b). Recent findings on the PSS-10 also showed similar descriptive findings for college students (Leppink et al., 2016; Klein et al., 2016).

Exclusion criteria are 1) self-reported severe symptoms of depression (as defined by a score higher than 20 on the Patient Health Questionnaire (PHQ-9) (Kroenke et al., 2001)) or 2) experiencing suicidal risk (as defined by a score of 2 or above on the PHQ-9 item nine or a score of 1 or above for the question “In approximately how many months during the past 12 did you think about how you might kill yourself or work out a plan of how to kill yourself?” or responding somewhat likely/very likely to the question of “How likely do you think it is that you will act on this plan in the next 12 months?”).

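### Interview question 2 presupposes that the student preferred internet-based over face-to-face support, which no listed question first establishes

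*Protocol article*

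**What the plan says.** Section 2.8.4 of the protocol article plans "in-depth interviews with a selection of at least 10 participants among the students who complete all main modules". Interviewees are chosen for maximum variation, so that low and high satisfaction, and small and large changes in perceived stress, are all represented. The questions come from earlier studies, and the article states: "The original questions have been revised to fit the purpose of our study". Ten numbered questions follow. The first asks about initial thoughts and feelings. The second is "Why did you prefer this program as an internet-based treatment over face-to-face support". The eighth returns to the delivery format: "What was your experience of the program being online and delivered via the internet". The tenth asks what the student would change or add.

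Under section 2.11 the interviews are recorded and transcribed, and the transcripts go into a thematic analysis together with the written responses.

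**The concern.** Question 2 asks for the reasons behind a preference without asking whether there was one. A student who had no preference, or who would rather have had face-to-face help, must reject the premise before answering. Some will do so. Others will oblige with a reason in favour of the online format.

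Feasibility and acceptability are the main objectives of the trial, and the interviews are one of the sources meant to explain them. If favourable reasons are partly prompted by the question, a theme on why students chose the online format is hard to interpret: the analyst cannot tell a volunteered preference from a supplied one.

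**Working it through.** No arithmetic applies. The check is whether the protocol establishes the premise anywhere, or gives grounds to doubt it.

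1. **Does an earlier question establish the preference?** No. Only question 1 precedes it, and that asks about first reactions to the program. None of the other nine questions asks whether the student preferred one format.

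2. **Does enrolment establish it?** No. Section 2.1 describes a single-group pre-test and post-test study, so the trial offers no face-to-face alternative to choose against. In section 2.10 the main recruitment route is a survey e-mailed to students, after which eligible students are invited. Other routes run through advisors, mentors, lecturers and advertisements. Agreeing to take part shows willingness to use the program, not a choice of it over face-to-face support.

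3. **Does the protocol give other reasons for using an online program?** Yes. Among the barriers to campus services, the Introduction lists "long waiting lists and insufficient resources to meet the increased demands on counseling centers at universities". A student who came for that reason may have preferred face-to-face help and been unable to get it.

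4. **Does it expect some participants to want face-to-face contact?** Yes. The Discussion names this among possible reasons for discontinuing. The support is limited, because interviewees must have completed all main modules and those who left for this reason will not be asked question 2. It still shows that the protocol does not take the preference as universal among those who enrol.

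5. **Can a student use both forms of support?** Yes. The exclusion criteria in section 2.4 cover severe depressive symptoms and suicidal risk only. Section 2.8.3.1 records current psychotherapy or medication as a sample characteristic. A student in psychotherapy can therefore enrol, complete the modules and be interviewed. For that student the program may be an addition to other help and not a substitute for it.

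**Reach.** One of ten questions is affected, in each of at least 10 interviews. The CSQ-8, the SUS-10, the adherence measures and the module evaluations are collected separately and do not depend on the wording of question 2.

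**The case against.** The best defence is that the harm is limited, and much of it stands.

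- Question 8 covers online delivery in neutral terms, question 1 is open, and question 10 invites criticism. A student who wanted face-to-face help has several places to say so. This softens the problem without removing it: question 8 asks about the experience of the format, not about the choice of it, and comes after the leading question.
- A semi-structured format allows follow-up, and a fuller topic guide may exist that is not shown. That is fair, and nothing here assumes that probes are absent. A probe that follows a leading premise does not withdraw it, however.
- Deliberate sampling of dissatisfied students and of those with little improvement works against one-sided themes. That stands.
- The Introduction also lists a preference for self-help and perceived stigma among the barriers to campus services, so the premise will be true for some students. That stands too. The point is only that it is not established for all.

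Three stronger readings are tempting, and the documents do not support them.

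- A reader might infer that the premise is false for students in psychotherapy. The protocol does not say that their therapy is face-to-face, and such a student may still have preferred online help for stress. It may be false for them; no more can be said.
- A reader might infer that the acceptability data as a whole are biased. Only interview answers on delivery format are exposed, and the protocol nowhere calls the interviews its main explanatory source.
- A reader might infer that question 7, "Were there any enjoyable parts in the program", is one-sided in the same way. It can be answered with a no. Questions 6 and 10 leave room for criticism, and the open questions after each module ask what the student would change.

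**Conclusion.** Question 2 is leading as printed, because it presupposes a preference that neither the question list nor the design establishes and that the protocol's own text makes doubtful for some interviewees. This is a minor wording flaw. It can affect what the thematic analysis says about the choice of an online format, and nothing else in the plan. Its effect cannot be put in figures.

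The conclusion assumes that interviewers ask the question broadly as printed. If an unseen topic guide already opens with whether there was a preference, the point falls away.

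**What to change.** Reword question 2 neutrally, for example: *Did you have a preference between internet-based and face-to-face support when you started, which one, and why?* Tell interviewers to accept as full answers that no choice was available, or that the student was using both.

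If interviews have already begun, record which wording each one used, so that answers about format can be read with that in mind.

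The cost is the rewording of one question and, if needed, one extra note per interview. No outcome, sample size or analysis changes.

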#### Assessments

2.8.5

Overview of the assessments can be seen in Table 1.

**Table 1 t0005:** Measures and assessment points.

	Assessment points		
	T0	Tx	T1
Socio-demographics	X		
Client Satisfaction Questionnaire (CSQ-8)			X
System Usability Scale (SUS-10)			X
Perceived Stress Scale (PSS-10)	X		X
Quality of life (EQ-5D-5L)	X		X
Perceived Stress Scale (PSS-4)		X	
Patient Health Questionnaire (PHQ-9)	X		X

T0 = Pre-test.

Tx = Weekly assessments.

T1 = Post-test (5-week).

### Sample size

2.9

There is no consensus on how to calculate the sample size of an open feasibility study. Some studies suggest a sample of at least 12 participants (Julious, 2005; Moore et al., 2011) while others recommend 35 or more participants (Teare et al., 2014). Thus, in the present study, no power calculation was conducted to determine the sample size, as we mainly focus on the feasibility and acceptability of the intervention. Based on the rule of thumb and similar previous studies (Rahmadiana et al., 2019), we anticipate that 50 participants will be sufficient to examine our main objectives. For semi-structured interviews, the sample size will depend on the saturation of the codes (Sim et al., 2018). However, we aim to reach at least 10 participants, since it is well-documented that code saturation can be reached after approximately 10 interviews (Hennink et al., 2017).

